### **1.5.2.4. Clinical Safety of Azithromycin and Chloroquine Combination in Pregnancy**

Both AZ and CQ have been widely used in all trimesters of pregnancy and are considered safe in pregnant women as individual agents. AZ has been used in all trimesters of pregnancy for STI and bacterial infections with dosage between 500 mg and 2000 mg. CQ was recommended for prevention and treatment of malaria in all trimesters of pregnancy until recently with CQ resistance becoming widespread and the treatment courses with less than 2000 mg CQ base (total dose) produced similar rates of adverse events.

A comprehensive review of the literature to identify publications describing the safety of CQ and AZ in pregnant women did not identify any additional safety issues beyond the information contained in the CQ and AZ product labels. In the doses used for malaria treatment and prophylaxis in pregnant women, an increased risk of adverse pregnancy outcomes has not been reported with CQ. With regard to AZ, many years of worldwide use, in addition to randomized trials and observational epidemiology studies have not identified any adverse pregnancy outcomes associated with AZ exposure during pregnancy.

To date there are no well-controlled clinical studies evaluating the effects of co-administration of AZ and CQ in pregnant women also containing safety information. In Pfizer trials where both drugs were used concomitantly for the treatment of uncomplicated malaria in adults, no additional safety concerns beyond those listed in the labels of the individual products were identified. No pharmacokinetic interaction is observed between the two drugs.

Please refer to the IB for additional information regarding the use of AZ and CQ combination in Malaria.

## 1.6. Rationale for AZCQ in IPTp

The benefits of current IPTp strategy are threatened by increasing resistance of *P. falciparum* to SP. Although review of SP efficacy data for pediatric treatment and IPTp suggests that SP may still offer some protection against malaria in pregnancy (MIP) in geographic areas where day 14 post-treatment failure rates for SP in children are as high as 39%, This protection, however, is not uniform across populations. Primigravidae, who are particularly vulnerable to the effects of MIP, are protected the least by SP in areas where SP sensitivity is on the decline. In Ghana, where parasite sensitivity to SP remains higher than in east and southern Africa, uncorrected parasitological failure rates by Day 28 post-treatment were 36.4% (32 of 88) in children, 27.1% (29 of 107) in primigravidae, 6.1% (3 of 49) in secundigravidae, and 3.8% (2 of 52) in multigravidae. Thus, SP is already compromised and an urgent need exists to identify alternative compounds for use in IPTp.

AZCQ offers several reasons for its evaluation as a potential replacement for SP in IPTp:

- 1) AZ and CQ combination is synergistic against CQ resistant strains of *P. falciparum* as demonstrated in vitro and in vivo;
- 2) Coadministration of AZ and CQ has demonstrated efficacy, safety and tolerability in two Phase 3 clinical studies (A0661134 and A0661155) in the treatment of symptomatic uncomplicated malaria in adults in sub-Saharan Africa;
- 3) AZ and CQ have been in market for several years and have extensive safety database in adults, children and pregnant women;
- 4) AZ and CQ have also been widely used in all trimesters of pregnancy and are considered safe in pregnant women as individual agents; and
- 5) Treatment and prevention of sexually transmitted infections including *T. pallidum* (syphilis), *N. gonorrhoeae* and *C. trachomatis* infections has been demonstrated to lower the incidence of adverse pregnancy outcomes by about 30%; hence, activity of AZ against these infections should provide additional benefit.

This study is a Phase 3 clinical trial aimed at demonstrating superiority of AZCQ over SP in countries in East and Southern sub-Saharan Africa, where SP is the current standard of care, and where SP resistance is a considerable issue. This will be the pivotal study for regulatory submissions to the EMA and to the national regulatory agencies in sub-Saharan African countries.

### 1.6.1. Dosing Regimen Selection

#### 1.6.1.1. Sulfadoxine-Pyrimethamine (SP) as Comparator

Although SP resistance is increasing especially in East and Southern Africa, it remains the WHO recommended treatment for IPTp throughout the region. SP will be administered in standard dosing regimen recommended for IPTp. Each subject will receive three IPTp treatment courses. The first course will be administered at the first antenatal visit in second trimester. The subsequent two courses will be administered at 4-8 weeks interval between courses in second/third trimester. Each treatment course will consist of a single oral dose of 1500 mg sulfadoxine and 75 mg pyrimethamine ie, 3 fixed dose tablets of SP (500 mg/25 mg strength). All treatment courses will be administered under supervision at the ANC clinic.

#### 1.6.1.2. Azithromycin-Chloroquine (AZCQ)

AZCQ will be administered as three IPTp treatment course regimens during second and third trimester. The first treatment course will be administered at the first ANC visit in second trimester. The subsequent two courses will be administered at 4-8 weeks interval between courses in second/third trimester. Each treatment course will consist of 3-day of dosing: 1000 mg AZ/620 mg CQ, ie, 4 fixed dose tablets of AZCQ (250mg/150mg strength) administered once daily for 3 days. First dose will be administered under supervision at the ANC; subsequent two doses will be administered at home under supervision of a field worker.

**Rationale for AZCQ Dosing Regimen:** The dosing regimen of AZCQ has been selected for the IPTp program for the following reasons:

1. The above 3-day dosing regimen (1000 mg AZ/620 mg CQ, ie, 4 fixed dose tablets of AZCQ (250 mg/150 mg strength) administered once daily for 3 days) was evaluated and demonstrated efficacy in two adult treatment clinical trials (A0661134 and A0661155) in sub-Saharan Africa. Both PCR corrected and uncorrected parasitological efficacy rates were above 90%. For details on studies A0661134 and A0661155 (Refer to Section 1.5.2.2. and the IB).
2. In a clinical pharmacology study in healthy subjects (A0661186), the pharmacokinetics of the fixed dose AZCQ combination tablet appeared to be comparable to that of the individual tablets of AZ and CQ used in earlier adult treatment trials (Refer to Section 1.5.2.1. and the IB).
3. Although pregnant women experience unique physiological changes that can alter drug disposition during gestation, available data and PK modeling suggests that AZ and CQ PK are not significantly different between pregnant and non-pregnant women.
4. A total AZ dose of 3000 mg to be used for each IPTp treatment course is higher than the 2000 mg dose needed for treatment of STIs including *T. Pallidum*, *C. trachomatis*, and *N. gonorrhoea*.

A fixed dose combination tablet formulation AZCQ has been developed for the IPTp clinical program. Each tablet is labeled to contain 250 mg AZ and 155 mg CQ base. Please note that the content of CQ base in this tablet is equivalent to that contained in the commercial tablets of CQ (Aralen, 150 mg CQ base) used in the previous studies (A0661134 & A0661155). CQ is present in these tablets in the form of its phosphate salt. The 5 mg difference in strength is explained by the use of slightly different (more accurate) CQ base potency factors for in the CQ phosphate salt than what is used for the Aralen tablets. The combination tablet uses the actual potency factor (62.0%) vs Aralen that uses an approximate number of 60% for potency factor.

## **2. STUDY OBJECTIVES AND ENDPOINTS**

### **2.1. Objectives**

The primary objective is to establish superiority of AZCQ over SP in protective efficacy for IPTp as measured by the proportion of subjects with sub-optimal pregnancy outcome.

Key secondary objectives include comparison of IPTp regimens of AZCQ and SP in:

1. Proportion of subjects with LBW (<2500 g) live neonates;
2. Proportion of subjects with severe anemia (hemoglobin <8 g/dL);
3. Proportion of subjects with anemia (hemoglobin <11 g/dl);
4. Proportion of subjects with placental parasitemia;
5. Occurrence of sexually transmitted infections (STIs); and
6. Safety and tolerability of the two treatment regimens.

### **2.2. Endpoints**

#### Primary Efficacy Endpoint

- Presence of subjects with a sub-optimal pregnancy outcome defined as any of the following: live-borne neonate (singleton) with low birth-weight (or LBW for short, defined as live birth weight <2,500g), premature births (<37 weeks), abortion ( $\leq$ 28 weeks), still birth (>28 weeks), lost to follow-up prior to termination of pregnancy or delivery, or missing birth weight of the neonates.

#### Key Secondary Efficacy Endpoints

1. Occurrence at birth of a LBW live neonates;
2. Occurrence of severe maternal anemia (Hb <8 g/dL) at 36-38 weeks of gestation;
3. Occurrence of anemia (Hb <11 g/dL) at 36-38 weeks of gestation;

4. Occurrence of placental parasitemia at delivery;
5. Occurrence of placental malaria as determined by histology;
6. Number of episodes of STIs per subject including *T. pallidum*, *N. gonorrhoeae*, *C. trachomatis*, during the study period following first dose (diagnosis based on clinical presentation any time from first IPTp dose to delivery and/or on laboratory test results between Weeks 36-38).

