#### **4.2. Exclusion Criteria**

Subjects presenting with any of the following will not be randomized in the study:

1. Age <16 years old or >35 years old.
2. Multiple gestations (more than one fetus) as per the ultrasound results at screening.
3. Clinical symptoms of malaria.
4. Hemoglobin < 8 g/dL (measured at baseline).
5. Any condition requiring hospitalization or evidence of severe concomitant infection at time of presentation.
6. Use of antimalarial drugs in previous 4 weeks.
7. History of convulsions, hypertension, diabetes or any other chronic illness that may adversely affect fetal growth and viability.
8. Inability to tolerate oral treatment in tablet form.
9. Known allergy to the study drugs (AZ, CQ, and SP) or to any macrolides or sulphonamides.
10. Present history of smoking or alcohol or drug abuse since first becoming aware of current pregnancy.
11. Participation in other studies within 30 days before the current study begins and/or during study participation.
12. Inability to comprehend and/or unwillingness to follow the study protocol.
13. Concurrent participation in another investigational study.
14. Previously randomized in this study.
15. Requirement to use medication during the study that might interfere with the evaluation of the study drug (eg, trimethoprim-sulfamethoxazole use in subjects positive for HIV infection) or is contra-indicated during pregnancy per package inserts.

16. Severe acute or chronic medical or psychiatric condition or laboratory abnormality that may increase the risk associated with study participation or investigational product administration or may interfere with the interpretation of study results and, in the judgment of the investigator, would make the subject inappropriate for entry into this study. Examples would include but not limited to:
  - a. Symptomatic HIV infection, including physical findings that suggest immunocompromised status (eg, oral candidiasis);
  - b. Neurological conditions which may predispose to complications during pregnancy, including seizure disorders;
  - c. Severe psychosis or major disorder that may interfere with the conduct of the study or adherence to study medication;
  - d. Known, clinically significant pre-existing renal or hepatic disease.
17. Evidence of current obstetric complications that may adversely impact the pregnancy and/or fetal outcomes, including presence of congenital anomalies, placenta previa or abruption.

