### **5.8. Treatment for Anemia in Pregnancy**

Subjects diagnosed with anemia at the baseline, Day 0 of Visit 1 or any other visits during the study period will receive the standard treatment according to local ANC guidelines.

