**Refer to Section 7 (Assessments) for details on the procedures performed in the study.**

### **6.1. Study Period**

#### **6.1.1. Visit 1: Baseline/Screening Visit/Treatment Course 1**

##### Day 0: Antenatal Care (ANC) Visit/Assessment of Study Eligibility

After informed consent is obtained, the subject must have the following procedures performed prior to the start of therapy:

- Medical history;
- Obstetrical history;
- Concomitant treatment history;
- Urine pregnancy test (if not done at any prior ANC visit for this pregnancy);
- Urine analysis for glucose and proteins;
- Complete physical examination;

- Vital signs;
- Routine obstetric checkup;
- Obstetrical ultrasound examination (if urine pregnancy test is positive);
- Hemoglobin level (with HemoCue™);
- *T. pallidum* screen test if not done at previous ANC check up;
- Nasopharyngeal swab test for macrolide resistant and penicillin resistant *Streptococcus pneumoniae* in approximately 600 subjects each in AZCQ and SP arms from 2 or more sites as feasible.

#### Day 0: Post Assessment of Eligibility/Treatment Course 1

Subjects who have met all inclusion/exclusion requirements and are eligible to be randomized will have the following procedures performed:

- Randomize to one of the study treatments;
- Administer treatment (AZCQ or SP);
- Assess adverse (AE) events;
- Provide LLINs.

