### 9.2.1. Analysis of Primary Endpoint

The primary efficacy endpoint of the trial is the presence of subjects with a sub-optimal pregnancy outcome defined as any of the following: live-borne neonate (singleton) with low birth-weight (or LBW for short, defined as live birth weight <2,500g), premature births (<37 weeks), abortion (≤28 weeks), still birth (>28 weeks), lost to follow-up prior to termination of pregnancy or delivery, or missing birth weight of the neonate. The primary analysis set will be the ITT, and will exclude multiple gestations. Secondary analyses will also be repeated using the per protocol analysis set.

Percentage of subjects with sub-optimal pregnancy outcome will be estimated for each treatment group. The following descriptive statistics will be available:

- Sample size (n) per group;
- Number of subjects with sub-optimal pregnancy outcome (m);
- Proportion of subjects with sub-optimal pregnancy outcome:

$$\hat{p} = \frac{m}{n}$$

- Two sided CI will be formed for the proportion of subjects using the normal approximation to the binomial:

$$\hat{p} \pm z_{1-\alpha/2} \sqrt{\frac{\hat{p}(1-\hat{p})}{n}}$$

The final results will be expressed in percentages, ie, proportions x 100. If the lower confidence limit is <0, it will be set to 0. If the upper confidence limit is >100%, it will be set to 100%.

The Mantel-Haenszel estimate of the common risk ratio will be computed using SAS Proc Freq, adjusted for the randomization strata. The risk ratio will be the proportion of AZCQ subjects with sub-optimal pregnancy outcome over the proportion of SP subjects with sub-optimal pregnancy outcome. The estimated variance for  $\ln(RR_{MH})$  given by Greenland and Robins will be utilized. The two-sided p-value will be calculated using the Wald test statistic on the natural log risk ratio scale.

Additional analysis models for the primary endpoint will be used to examine the interaction of a range of effects with treatment group. These effects include randomization strata, HIV status at baseline, age, and country. An alpha level of 0.05 2-sided will be used for these additional analyses.

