### 9.2.2. Analysis of Secondary Endpoints

The proportion of subjects with LBW is a key secondary endpoint. It is defined as the following: live-borne neonate (singleton) low birth-weight (or LBW for short, defined as live birth weight <2,500g). A secondary analysis will also be repeated using the per protocol analysis set.

All secondary efficacy endpoints that are dichotomous, expressed as a proportion, will be summarized and analyzed using the same methods as for the primary endpoint. Secondary efficacy endpoints that are not dichotomous will be analyzed using analysis of covariance (ANCOVA) when a baseline value is available, and analysis of variance (ANOVA) otherwise. The ANCOVA model will contain baseline as a covariate, as well as factors for treatment group and randomization strata. The ANOVA model will contain factors for treatment group and randomization strata.

For subjects with nasopharyngeal swabs positive for macrolide resistant and penicillin resistant *Strep. pneumoniae* (to be performed in about 600 subjects in each AZCQ arm and SP arm from at least 2 sites), the proportion positive at Baseline, Day 28-42 post delivery, and at 6 months post last AZCQ IPTp course will be computed. A listing of these subjects will also be provided.

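### The key secondary analysis of anemia (Hb <11 g/dL) at 36-38 weeks leaves out the baseline hemoglobin the trial already measures; the comparison stays valid but loses precision

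*Protocol*

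**What the plan says.** Section 2.2 of the protocol lists as key secondary endpoint 3 "Occurrence of anemia (Hb <11 g/dL) at 36-38 weeks of gestation". It sets no condition on hemoglobin at entry.

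The only numerical hemoglobin exclusion in Section 4.2 is "Hemoglobin < 8 g/dL (measured at baseline", so a woman with Hb 8 to <11 g/dL is eligible. Section 5.8 expects such women, since it provides local-guideline treatment for "Subjects diagnosed with anemia at the baseline, Day 0 of Visit 1" or later. The Visit 1 procedures in Section 6.1.1 include "Hemoglobin level (with HemoCue™") before therapy starts.

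On analysis, Section 9.2.2 states: "All secondary efficacy endpoints that are dichotomous, expressed as a proportion, will be summarized and analyzed using the same methods as for the primary endpoint". The primary method in Section 9.2.1 is "The Mantel-Haenszel estimate" of the common risk ratio, adjusted for the randomization strata, with the Greenland-Robins variance and a Wald test on the log scale. Section 4.3 makes gravidity, at two levels, the only randomization stratum.

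For non-dichotomous endpoints that have a baseline value, Section 9.2.2 prescribes a different approach: "The ANCOVA model will contain baseline as a covariate, as well as factors for treatment group and randomization strata". Continuous hemoglobin at 36-38 weeks, listed among the other secondary endpoints, is therefore adjusted for baseline. The key secondary endpoint cut from the same measurement is not.

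**The concern.** Baseline hemoglobin should be a strong predictor of whether a woman is below 11 g/dL at 36-38 weeks, and it has to be known for eligibility. The protocol accepts its value when hemoglobin is analyzed as a number, then sets it aside when hemoglobin is cut at 11 g/dL for a higher-ranked endpoint. No reason is given.

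Outcome variation that baseline could explain is left in the standard error of a key secondary comparison. The interval is wider than it need be, and a true effect on anemia is somewhat more likely to be missed. The method is also fixed in the text for all dichotomous secondary endpoints, so this is a stated choice rather than a detail left open.

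**Working it through.** **1. The plan's own figures.** The protocol gives no power, event rate or sample size for either anemia endpoint. Its only sample sizes are those in Table 4, for the primary endpoint. They reproduce with

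N = 2θ²[(1−p)/p + (1−q)/q] / (ln 0.80)², q = 0.8p,

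where θ = 4.556 is the group-sequential drift for one-sided alpha 0.000625, 90% power, looks at 50/70/100% and gamma(−4) spending. For p = 0.28: 2 × 4.556² × (2.571 + 3.464) / 0.0498 ≈ 5,033, against 5,044 in the table. Across the table the formula gives 5033/4195/3544/3023/2596 against 5044/4206/3552/3030/2602 (p = 0.44 was tried for the open top interval). All are within about 0.3%, so the design figures are not in question.

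**2. Inputs for the anemia endpoint.** From the protocol: 1:1 allocation, N between 2,602 and 5,044, one-sided alpha 0.025 for secondary endpoints, entry at Hb ≥8 g/dL. Assumed, because the protocol gives nothing: baseline mean 10.4-11.4 g/dL, SD 1.3 at both times, week 36-38 mean 0.2 higher, bivariate normal, correlation r = 0.3-0.6. Under these assumptions about 38-67% of enrolled women are below 11 g/dL at entry.

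**3. Variance formula (Greenland-Robins).** In each stratum of size n with two equal arms, let a and c be the AZCQ and SP events. Then

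Var(ln RR) = Σ[(a+c)/4 − ac/n] / [(Σa/2)(Σc/2)].

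**4. Worked case.** Baseline mean 10.8, r = 0.5, N = 5,044. The fraction below 11 at entry is 0.554. SP risk at 36-38 weeks is 0.638 in those women and 0.312 in the rest, so 0.4926 overall. RR = 0.920 gives about 80% power without adjustment.

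- No baseline stratification: a = 1143.0, c = 1242.3. Numerator 596.3 − 281.5 = 314.8; denominator 571.5 × 621.2. Variance = 0.000887.
- Split at 11 g/dL: numerator (427.9 − 261.6) + (168.5 − 50.4) = 166.3 + 118.1 = 284.3; same denominator. Variance = 0.000801.
- Reduction: 1 − 0.000801/0.000887 = 9.7%. This equals 1/(1 − 0.097) − 1, or about 11% more women.
- Power: |ln 0.920| / √0.000801 − 1.96 = 0.0834/0.0283 − 1.96 ≈ 0.99, or about 84% instead of 80%.

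Gravidity is omitted from both sides to isolate the effect of baseline Hb.

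**5. Range.**

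| r | Variance cut, split at 11 | Variance cut, five categories | Power from 80% (split at 11) |
|---|---|---|---|
| 0.3 | about 3% | about 4-5% | about 81% |
| 0.5 | about 9-10% | about 13-14% | about 84% |
| 0.6 | about 14-15% | about 20% | about 86% |
| 0.7 | not used | about 29% | not computed |

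The power gain is nearly the same at N = 2,602 and N = 5,044.

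**6. Bias check.** In 20,000 simulated trials (RR 0.90, N = 5,044, r = 0.5), the mean ln(RR) was −0.1057 unstratified and −0.1056 stratified, against a true −0.1054. The empirical variance fell by 9.2%. With 1:1 allocation the Mantel-Haenszel weights are close to one half in every stratum, so both analyses estimate the same overall risk ratio.

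**7. Severe anemia.** For key secondary endpoint 2, "Occurrence of severe maternal anemia (Hb <8 g/dL) at 36-38 weeks of gestation", the same model shows baseline explaining 0.1-0.8% of outcome variance with the split at 11, and 0.3-4% with 20 bins. That is close to nothing.

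**The case against.** The strongest reply is that nothing here is wrong. Prevalence of anemia at a fixed late visit is a legitimate endpoint, and Section 2.1 frames the objective as a proportion of subjects. Section 1.2 gives clearing existing parasitemia as one of the two aims of IPTp, so a woman anemic at entry and still anemic at 36-38 weeks can be a genuine failure of the regimen. Adjusting for randomization strata only is conventional, the Wald standard error already allows for chance imbalance in baseline hemoglobin, and a baseline-adjusted analysis of continuous hemoglobin is planned. Section 9 also lets the SAP modify the plan. All of this stands, except that the last point does not remove the issue: the protocol does prescribe a method for this endpoint, and that method omits baseline.

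Three stronger readings are tempting and should be resisted.

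- A reader might infer that the comparison is biased. Randomization protects it, and the simulation shows the same estimate either way.
- A reader might infer that most Hb <11 events are merely left over from entry. In the worked case women below 11 at entry supply 0.554 × 0.638 / 0.4926 = 72% of SP events, but they would supply 55% with no correlation at all, simply because they are 55% of the sample. The share does not measure carry-over.
- A reader might extend the point to Hb <8. Women below 8 g/dL are excluded at entry, and the gain there is negligible.

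The size is also open to challenge. Entry at 14-26 weeks leaves roughly 10-24 weeks to the 36-38 week visit, and anemia is treated in between. Both could lower the correlation, so the figure at r = 0.7 is an upper case.

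**Conclusion.** The point holds for Hb <11 g/dL as a loss of precision in a key secondary analysis. Validity, the primary endpoint and the sample size are unaffected. Under the stated assumptions the avoidable variance is about 3-15% with a single split at 11 g/dL, or 4-20% with five categories, for correlations of 0.3-0.6. With the single split, a comparison with 80% power would gain about 1 to 6 points. None of these sizes can be derived from the protocol; the direction does not depend on them as long as baseline and week 36-38 hemoglobin are positively correlated. This is a modest improvement at almost no cost, and it makes the dichotomous analysis consistent with the protocol's own ANCOVA.

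**What to change.** Add one sentence to Section 9.2.2, for Hb <11 g/dL at 36-38 weeks only: the Mantel-Haenszel risk ratio and its Greenland-Robins variance will be computed over strata formed by gravidity and baseline Hb category, for example 8 to <9, 9 to <10, 10 to <11, 11 to <12 and ≥12 g/dL. Fix the categories before any unblinded look at the data. In addition, report the endpoint descriptively for women with baseline Hb <11 and ≥11 g/dL, so that persisting and new anemia can be told apart. Leave the Hb <8 analysis as it is.

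The change needs no new data, visits, alpha or clinical rule. Baseline Hb should be available for every enrolled woman because eligibility depends on it. Section 6 allows results from an earlier antenatal visit to stand in for required tests, so the sentence should also say which value counts as baseline.
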